### Data Collection and Clinical Outcomes

Standard demographic, clinical and laboratory data (including medication details) will be collected prospectively from electronic medical records. Recipients are advised to receive routine follow-up weekly in months 0–3, every 2 weeks in month 4–6, monthly within 6–12 months, and every 3 months thereafter.

The general aim of this study is to determine the safety of metformin and empagliflozin in kidney transplant recipients and explore the role of metformin and empagliflozin treatment in improving metabolic profiles. Based on previous study, visceral-to-subcutaneous fat area ratio, evaluated by magnetic resonance imaging (MRI), is generally reported as a surrogate for metabolic risk and is markedly raised in patients with long-term exposure to steroids (23, 24). Hence, the primary outcome is the differences in the visceral-to-subcutaneous fat area ratio over 12 months among three groups. The visceral-to-subcutaneous fat area ratio will be measured at transplantation, and post-transplant 3, 6, 9, and 12 months. Kidney graft function will be evaluated when they receive routine follow-up. Secondary outcomes included glycometabolism (fasting plasma glucose, fasting insulin levels, 2-h post-prandial insulin levels, hemoglobin A1c, and insulin beta-cell function [indicated by the homeostasis model assessment of β cell function]), lipid metabolism (serum triglyceride, non-high-density lipoprotein, low-density lipoprotein, total cholesterol), inflammatory parameters (C-reactive protein, interleukin-6, and tumor necrosis factor alpha) (Table 1). We will also examine cardiovascular disease and microvascular complications, including the following: major adverse cardiovascular events; all-cause mortality; atherosclerotic cardiovascular (ASCV) death; hospitalization or death from coronary artery disease, ischemic stroke, or heart failure; observable background diabetic retinopathy; and diabetic peripheral neuropathy.

**Table 1 T1:** Routine follow-up.

**Visit**	**V0**	**V1**	**V2**	**V3**	**V4**
Time, days after kidney transplantation	−7day to 0 day	3 month	6 month	9 month	12 month
Participant-related information	×				
Informed consent	×				
History	×				
Inclusion/Exclusion	×				
Clinical examination	×	×	×	×	×
Efficacy and safety outcomes	×	×	×	×	×
Body weight	×	×	×	×	×
Height	×	×	×	×	×
Waist circumference	×	×	×	×	×
Visceral adipose tissue (VAT)	×	×	×	×	×
Subcutaneous adipose tissue (SAT)	×	×	×	×	×
VAT/SAT ratio	×	×	×	×	×
Glycometabolism	×	×	×	×	×
Fasting plasma glucose function	×	×	×	×	×
Fasting insulin levels	×	×	×	×	×
2-h postprandial insulin levels	×	×	×	×	×
Hemoglobin A1c	×	×	×	×	×
Insulin beta-cell function	×	×	×	×	×
Lipid metabolism	×	×	×	×	×
Serum triglyceride	×	×	×	×	×
Non-high-density lipoprotein	×	×	×	×	×
Low-density lipoprotein	×	×	×	×	×
Total cholesterol	×	×	×	×	×
Inflammatory parameters	×	×	×	×	×
C-reactive protein	×	×	×	×	×
Interleukin-6	×	×	×	×	×
Tumor necrosis factor alpha	×	×	×	×	×
Kidney graft function	×	×	×	×	×
Serum creatinine		×	×	×	×
Estimated glomerular filtration rate (eGFR)		×	×	×	×

### Sample Size Estimation

Sample size calculation is based on the primary outcome. According to the previous study, the visceral-to-subcutaneous adipose tissue area ratio was 0.83 (SD = 0.48; *n* = 58) for kidney transplant recipients (25). The ratio is estimated to be half of that in the intervention group. The estimated sample sizes for 90% power at 5% significance is 28 patients in each group. Considering an estimated 20% dropout rate, we assure that the sample size exceeds the minimal number needed to ensure the validity of the mean, effect size and rationale of feasibility. Therefore, 105 individuals (35 each group) are expected to be enrolled.

### Statistical Analysis

Two populations will be used in the analyses. The intention-to-treat (ITT) population will include all participants who have been randomly assigned, whereas the per-protocol (PP) population will include all participants who accomplish the entire intervention. The baseline characteristics of the study will be summarized as the means ± standard deviations for parametrically distributed data, geometric mean values (and 95% confidence intervals) for non-parametrically distributed data, and numbers (percentages) for categorical data.

Differences between participants who complete and withdraw from the trial will be analyzed by using a Student *t*-test or the Mann–Whitney test for continuous variables (e.g., age) and the chi-squared test for categorical variables (e.g., sex). For clinical outcomes, analysis of covariance will be used to examine differences among three groups, adjusting for potential confounding factors and effect modifiers (e.g., baseline age and sex). Based on the literature, some patients have higher risk of post-transplantation diabetes mellitus (PTDM), including those with family history of diabetes; or polycystic kidney disease; or age ≥60 years; or age 45–59 years plus (i) triglycerides ≥200 mg/dL; (ii) triglycerides 150–200 mg/dL and body mass index >27 kg/m2; (iii) triglycerides 150–200 mg/dL and high density lipoprotein (HDL) <40 mg/dL (men)/ <40 mg/dL (women) Hence, subgroup analysis will be conducted based on the risk of PTDM, and was also conducted based on the components of the criteria for high-risk PTDM (26–28). Our statistical analysis will be performed by using R software, and the results will be considered significant at a *P*-value of < 0.05.

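### ANCOVA is named for clinical outcomes without being limited to continuous ones, although the listed outcomes include sparse yes/no events; the baseline fat ratio is also not named as a covariate

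*Protocol article*

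**What the plan says.** All references are to the protocol article.

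- **Method.** Statistical Analysis: "For clinical outcomes, analysis of covariance will be used to examine differences among three groups". Two covariates are mentioned, and only as examples: "adjusting for potential confounding factors and effect modifiers (e.g., baseline age and sex". No measurement scale is stated. The chi-squared test appears in that section only for comparing patients who complete with those who withdraw. Geometric means appear only for describing baseline data.
- **Outcomes.** The section headed "Data Collection and Clinical Outcomes" gives the primary endpoint as follows: "the primary outcome is the differences in the visceral-to-subcutaneous fat area ratio over 12 months among three groups". It then lists continuous metabolic and inflammatory measures, and after these the further outcomes "major adverse cardiovascular events; all-cause mortality; atherosclerotic cardiovascular (ASCV) death; hospitalization or death from coronary artery disease, ischemic stroke, or heart failure", with retinopathy and peripheral neuropathy. Table 1 schedules the fat ratio at V0 and at 3, 6, 9 and 12 months.
- **Planning.** Sample Size Estimation: "the visceral-to-subcutaneous adipose tissue area ratio was 0.83 (SD = 0.48" in an earlier study. The assumed effect is a halving: "The ratio is estimated to be half of that in the intervention group". The stated size of 28 per group, for 90% power at the 5% level, is raised to 35 for 20% dropout.

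**The concern.** The analysis sentence applies to a class of outcomes whose name matches the heading under which both continuous measures and events are listed. Taken as written, deaths and cardiovascular events would be compared by a linear model that assumes a continuous outcome with similar variance in each arm. An arm without events has zero variance, so that assumption fails in the very situation a trial of this size is likely to meet. Safety is part of the stated general aim. A P-value on death or cardiovascular events that falls on one side of 0.05 under the linear model and on the other under an exact test would be hard to defend.

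For the primary ratio, the baseline value of the same variable is usually the most useful covariate. It is collected, but the examples given are age and sex.

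**Working it through.** **1. The plan's own sample size.** Inputs from Sample Size Estimation: means 0.83 and 0.83/2 = 0.415, difference 0.415, SD 0.48, two-sided 5% (sidedness assumed), power 90%.

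n = 2 × (1.960 + 1.282)² × 0.48² / 0.415² = 28.1, so 29 when rounded up, against 28 stated. Power at 28 is 89.9% (normal approximation) or 88.8% (t-test). 28/0.8 = 35 and 3 × 35 = 105. The figure is reproduced as a two-arm, additive comparison of means with a common SD.

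**2. How sparse events may be.** The article gives no event rate for this trial. Its Discussion cites cardiovascular death rates of 0.28 to 0.96 per 100 patient-years, all beyond year 1. For 105 patient-years that is 0.29 to 1.01 deaths. This is only a rough guide: it leaves out the first year and non-fatal events.

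**3. Linear model against exact test.** Hypothetical counts, 35 per arm, no covariates.

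Events 3, 0 and 0:
- Between-arm sum of squares: 35 × [(2/35)² + 2 × (1/35)²] = 0.1714, on 2 df.
- Within-arm sum of squares: 3 × 32/35 = 2.743, on 102 df.
- F = (0.1714/2)/(2.743/102) = 3.19, P = 0.045.
- Exact P = 3 × C(35,3)/C(105,3) = 3 × 6,545/187,460 = 0.105.
- Pearson chi-squared P = 0.046.

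Events 4 and 0 in two arms: t-test P = 0.040, Fisher P = 0.114, Pearson chi-squared P = 0.039.

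**4. True type I error.** Enumeration over three binomial arms of 35 with a common event rate, nominal 5%:

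| Event rate | Linear model | Exact test |
|---|---|---|
| 1% | 0.8% | 0.06% |
| 2% | 2.4% | 0.4% |
| 5% | 3.7% | 2.3% |
| 10% | 4.5% | 3.9% |

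**5. Scale of the primary ratio.** CV = 0.48/0.83 = 0.58. A normal model with SD 0.48 puts 4.2% of values below zero at mean 0.83 and 19.4% at mean 0.415, which cannot occur for an area ratio. *Assume* instead a lognormal ratio with the same CV in each arm: log SD = √ln(1 + 0.58²) = 0.537, using the unrounded CV. Simulated two-arm t-tests, 28 per arm:

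| Reduction | Untransformed | Log |
|---|---|---|
| none (type I error) | 4.8% | 4.9% |
| 25% | 45% | 50% |
| 30% | 63% | 69% |
| 40% | 90% | 94% |
| 50% (planned) | 99% | 99–100% |

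On the log scale the planned halving would need ln 2/0.537 = 1.29 SD, or 13 per arm (14 by t-test), so the change of scale does not threaten the stated 28.

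**6. Baseline ratio as covariate.** Three-arm ANCOVA simulation under the same lognormal assumption, 28 per arm, 30% reduction, pairwise power. With a baseline-to-follow-up correlation of 0 (no information in the baseline) it was 66% untransformed and 69% log. With an assumed correlation of 0.6 it was 82% and 86%. The article gives no correlation, so this is an illustration.

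**The case against.** Several objections are fair, and most of them limit the point without removing it.

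- *The sentence was meant for continuous outcomes.* The events come after the listed secondary outcomes, as something also to be examined, with no hypothesis or power attached. That may be the intention. But the sentence carries no such limit, the section heading covers both kinds of outcome, and no other between-arm method is given. The same section separates continuous from categorical variables for completers against withdrawals, so the distinction was available.
- *The P-values in step 3 show false positives.* A reader might infer this, and it does not follow. Pearson chi-squared, a standard test for binary data, gives almost the same values as the linear model (0.046 and 0.039). Step 4 shows the linear model staying below 5% at every rate tried. Much of the gap is the conservatism of the exact test.
- *The plan prescribes untransformed analysis of every outcome, and this is invalid for the fat ratio.* The text says neither. ANCOVA of log values is still ANCOVA, and the scale can properly be left to an analysis plan that is not shown. That the sample size reproduces additively concerns planning, not the model. Skewness is inferred from the CV and the zero bound, and is not reported. Type I error holds on both scales.
- *The covariates are only examples.* True: the baseline ratio is not excluded. It is simply not named.

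**Conclusion.** The point holds as a defect of wording with a specific remedy. ANCOVA is the only between-arm method named, and it is not limited to continuous outcomes although sparse binary events are among those listed. Individual P-values can differ materially from exact ones (0.045 against 0.105 with three events in one arm), but inflated type I error is not shown at event rates of 1% to 10%. The example counts are hypothetical, because the article gives no event rate for the trial.

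Naming the baseline ratio as a covariate is a gain at no cost in data; its size depends on a correlation that the article does not give. The log scale is a modest gain in efficiency, about 4 to 6 points of power for reductions of 25% to 40%. It rests on an assumed lognormal distribution, which favours the log by construction. For the planned halving the choice of scale hardly matters. Nothing here puts the stated sample size or the validity of the primary comparison in doubt.

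**What to change.** 1. Restrict the ANCOVA sentence to continuous outcomes.
2. For cardiovascular events, death, hospitalisation, retinopathy and neuropathy, report counts per arm with exact confidence intervals and Fisher's exact test (or Firth logistic regression), labelled descriptive.
3. Name the baseline VAT/SAT ratio as a covariate in the primary ANCOVA.
4. Optionally, make ln(VAT/SAT), adjusted for the log baseline ratio, the primary scale. Report ratios of geometric means with 95% confidence intervals, and keep the untransformed analysis as a sensitivity analysis.

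All four are changes of wording, with no effect on enrolment, visits or data collection. Item 2 accepts a conservative test for the events, which suits a descriptive label. The price of item 4 is that the effect is reported as a ratio and not as an absolute difference. The scale should be fixed before outcome data are examined.

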### Procedures

Metformin is administered 500 mg twice daily orally from discharge based on the previous preliminary clinical trial (17). Empagliflozin is administered 25 mg once daily orally from discharge (18, 20). This will commence at randomization and continue for 12 months. The decision to continue with metformin beyond 12 months of follow-up is left to the discretion of the caring physician. In addition, during the follow-up, when kidney transplant recipients are diagnosed with PTDM, insulin therapy were adopted to reduce the glucose level at 6.1–6.7 mmol/L based on Chinese Management Guideline of post-transplantation diabetes mellitus after kidney transplantation (21).

Immunosuppressive regimen has been reported in our previous study (22). In brief, all participants will receive standardized triad immunosuppression, consisting of tacrolimus, mycophenolate mofetil/enteric-coated mycophenolate sodium, and steroids. Tacrolimus trough levels are measured by the enzyme multiplied immunoassay technique before breakfast and dose administration in the morning. Recommended tacrolimus trough levels are 5–10 ng/ml. MMF is started at 1000 mg one night before operation and maintained at 1000 mg twice daily with area under curve of mycophenolate mofetil maintained at 30–70 mg/h·L-1. If EC-MPS is selected, 720 mg is given the night before surgery and 720 mg bid thereafter. Methylprednisolone is injected intravenously at 500 mg during the operation and 200 mg per day 3 days after the operation. Then 60 mg prednisone is initiated, and gradually taper to 5–10 mg per day for maintenance.

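### The ANCOVA selects covariates by an open confounder rule and does not name the baseline VAT/SAT ratio, so precision available from scans already scheduled may be lost

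*Protocol article*

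**What the plan says.** The Statistical Analysis section gives one rule for all clinical outcomes, the primary included: "analysis of covariance will be used to examine differences among three groups", "adjusting for potential confounding factors and effect modifiers (e.g., baseline age and sex". Age and sex are examples, and the list is not closed. The baseline VAT/SAT ratio is neither named nor ruled out.

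Data Collection and Clinical Outcomes defines the endpoint: "the primary outcome is the differences in the visceral-to-subcutaneous fat area ratio over 12 months among three groups". It does not say whether this means the month-12 value, the change from baseline or a summary over visits. The ratio "will be measured at transplantation, and post-transplant 3, 6, 9, and 12 months", and Table 1 places the first scan at visit V0, day −7 to day 0. Under Procedures, both study drugs start at discharge (for example, "Metformin is administered 500 mg twice daily orally from discharge"), so the V0 scan precedes treatment.

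Sample Size Estimation uses the raw spread of the ratio ("the visceral-to-subcutaneous adipose tissue area ratio was 0.83 (SD = 0.48") and plans for a large effect: "The ratio is estimated to be half of that in the intervention group". It takes no credit for baseline adjustment.

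**The concern.** Randomisation already removes systematic confounding. Covariates in the primary model serve to reduce residual variance and to correct chance imbalance in prognostic factors. A rule that looks for potential confounders points the analyst to a different question. Effect modification is also a separate matter, since it is examined through interaction terms rather than by adding a covariate. Because the list is open, covariates could be chosen after the data are seen, and the trial is open label.

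The baseline value of the outcome is the natural candidate for a precision covariate, and it is already being collected. It matters here because the planning SD of 0.48 is 58% of the mean of 0.83 (0.48/0.83), so the trial is powered only for roughly a halving of the ratio. If the baseline ratio is left out, smaller effects that the same patients could have shown may be missed.

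**Working it through.** **Inputs from the article.** Control mean 0.83; SD 0.48; planned difference 0.83/2 = 0.415; power 90%; significance 5% (two-sided assumed, as sidedness is not stated); 28 evaluable per arm; 20% dropout; 35 per arm, 105 in total.

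**Assumed.** Correlation r between baseline ratio and follow-up ratio: not given in the article, so taken as 0.3 to 0.8.

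**Step 1: the plan's own figure.** n per arm = 2 × [0.48 × (1.960 + 1.282)/0.415]² = 28.11. The article states 28; strict rounding up gives 29. Power at 28 is 89.9% by the normal approximation and 88.8% by the noncentral t. Then 28/0.80 = 35 per arm and 3 × 35 = 105. The plan reproduces as an unadjusted comparison of two means at one time.

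**Step 2: effect of adjusting for baseline.** Residual SD = 0.48 × √(1 − r²), so variance falls by r². By the normal approximation, the difference detectable with 90% power is 3.242 × 0.48 × √(1 − r²) × √(2/28), which is 0.416 at r = 0. The table gives the noncentral-t values for 28 per arm. They are slightly larger and ignore the one degree of freedom spent on the covariate. The last column is power for a 30% reduction (0.30 × 0.83 = 0.249), an effect chosen only for illustration.

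| r | Fall in variance | Detectable difference (normal) | Detectable difference (noncentral t) | As % of 0.83 | Power for 0.249 |
|---|---|---|---|---|---|
| 0 (no covariate) | 0% | 0.416 | 0.423 | 51% | 48% |
| 0.3 | 9% | 0.397 | 0.404 | 49% | 52% |
| 0.5 | 25% | 0.360 | 0.367 | 44% | 60% |
| 0.7 | 49% | 0.297 | 0.302 | 36% | 76% |
| 0.8 | 64% | 0.250 | 0.254 | 31% | 89% |

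**Step 3: the comparator.** The first row has no covariates, but the article mentions age and sex. If these explained 10%, 20% or 30% of the variance (assumed; not in the article), starting power for 0.249 would be 52%, 57% or 62% rather than 48%. The gain from adding baseline would then be smaller than the table suggests.

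**Step 4: change from baseline.** If the endpoint were analysed as change without baseline as covariate, the variance factor would be 2(1 − r): 1.4 at r = 0.3, 1.0 at r = 0.5 and 0.6 at r = 0.7. The factors with the covariate, 1 − r², are 0.91, 0.75 and 0.51. Using the baseline scan through a change score therefore does not replace adjusting for it.

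**Step 5: the interim scans.** With complete data, an unstructured repeated-measures model with arm-by-visit and baseline-by-visit terms gives the same month-12 contrast as a month-12 ANCOVA. A check on 84 simulated patients gave a standard error of 0.2072 under both. A gain at month 12 comes mainly from patients with earlier scans but no month-12 scan. The planned dropout is about 0.20 × 35 = 7 per arm, but the article does not say how many of these would have earlier scans, so this gain is not sized here.

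**The case against.** The strongest reply is that the article is condensed. Its covariate examples leave room for the baseline ratio, and a full protocol or analysis plan may name it. That stands in part: a reader might infer that the plan adjusts for age and sex and omits the baseline ratio, but the examples do not support that. What remains is the rule the article does state. An analysis plan that followed it faithfully would still choose covariates on a confounding criterion.

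A reader might also infer that the primary model is a single-visit ANCOVA that throws away the 3, 6 and 9-month scans and drops anyone without a month-12 scan. The article does not say this. Its endpoint wording fixes no visit, and the intention-to-treat population is defined as everyone randomised.

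On size, a high correlation cannot be presumed. The baseline scan is taken at transplantation, and the article itself says that long-term steroid exposure raises the ratio markedly. At r = 0.3 the gain is small. For the planned difference of 0.415, power without any covariate is already about 89% to 90%. All of this stands. It limits the size of the point but does not remove it.

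**Conclusion.** The point holds in a limited form. The stated covariate rule has the wrong purpose for a randomised comparison and does not name a pre-treatment covariate scheduled for every patient. If the baseline ratio were left out, the loss would be of precision, without bias. With 28 per arm, adjusting for it would lower the detectable difference from about 0.42 to about 0.40 at r = 0.3 and about 0.25 at r = 0.8. These figures rest on an assumed r, a two-sided 5% test and a comparator without covariates; against a model with age and sex the gain is smaller.

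Three stronger conclusions do not follow: that the plan excludes the baseline ratio, that it discards the interim scans, or that the sample size is wrong. The stated 28 per arm reproduces to within one patient and does not depend on this point. The change is worth making because it costs nothing, not because the analysis would otherwise be invalid.

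**What to change.** Replace the open confounder and effect-modifier wording with a fixed covariate set for the primary model: baseline VAT/SAT ratio, age and sex. Adjust each continuous secondary outcome for its own baseline where one is collected. Table 1 marks no V0 value for serum creatinine or eGFR, so those two need a separate statement.

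Optionally, specify a repeated-measures model of the 3, 6, 9 and 12-month ratios with arm, visit, arm-by-visit, baseline ratio, baseline-by-visit, age and sex, with the month-12 arm contrasts as primary. Its benefit lies mainly with patients who have earlier scans but miss month 12.

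The cost is a change of wording before the data are analysed. It needs no further scans or patients and leaves the stated sample size unchanged.

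### Subgroup analyses by PTDM risk and by each of its components fall under one P<0.05 rule in a trial too small to support them, and the HDL criterion prints the same limit for men and women

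*Protocol article*

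**What the plan says.** All of this is in the Statistical Analysis section of the protocol article unless another section is named.

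- The section defines high PTDM risk by family history of diabetes, polycystic kidney disease, age 60 or over, or age 45–59 with one of three lipid or BMI conditions. It then states that "subgroup analysis will be conducted based on the risk of PTDM" and that this "was also conducted based on the components of the criteria for high-risk PTDM".
- The third condition for ages 45–59 is triglycerides of 150–200 mg/dL with "high density lipoprotein (HDL) <40 mg/dL (men)/ <40 mg/dL (women").
- For clinical outcomes, "analysis of covariance will be used to examine differences among three groups".
- One threshold closes the section: "the results will be considered significant at a" P-value below 0.05. No other threshold or status is given for the subgroup results.
- Sample Size Estimation plans only the primary comparison: "the visceral-to-subcutaneous adipose tissue area ratio was 0.83 (SD = 0.48"), and "The ratio is estimated to be half of that in the intervention group". This leads to 28 patients per group for 90% power at 5%, and 35 per group (105 in total) with 20% dropout.
- Study Design limits age to over 18 and under 65 years.

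**The concern.** Two separate matters arise.

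**Subgroups.** The plan commits to one composite factor and to each of its components, and judges them by the same P<0.05 rule as the main result. Several components are narrow by construction. With eligibility ending below 65, the age 60 or over component covers only ages 60–64. Three others need age 45–59 plus a lipid or BMI condition. In a trial of 28–35 per arm, a nonsignificant component result would say almost nothing, and a significant one could easily be chance. The risk is that a reader takes either as evidence about who benefits.

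**HDL limit.** A criterion split by sex with the same value on both sides contradicts its own form. It is part of the high-risk definition, so it classifies patients, and the analyst needs to know which limits apply.

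**Working it through.** **1. The plan's own figure.** Inputs from Sample Size Estimation: mean 0.83, halved, so a difference of 0.415; SD 0.48; 90% power; 5% level (two-sided assumed).

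n per group = 2 × [0.48 × (1.960 + 1.282) / 0.415]² = 28.1, against 28 stated.

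Dropout: 28 / (1 − 0.20) = 35 per group, and 3 × 35 = 105. The figures reproduce. They cover the primary comparison and nothing else.

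**2. Number of subgroup factors.** One composite plus six components as printed makes seven. If the age 45–59 class counts as a single component, there are four components and five factors.

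**3. Cell sizes and power inside a subgroup.** The article gives no prevalence for any component, so this is a range over assumed values. Cell size = prevalence × 28 (completers) to prevalence × 35 (enrolled). Power is for a two-arm t-test of the full effect (0.415, SD 0.48, two-sided 5%), with cells rounded to whole patients and at least two per arm.

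| Assumed prevalence | Patients per arm | Power for 0.415 |
|---|---|---|
| 5% | 1.4–1.8 | 8% |
| 10% | 2.8–3.5 | 13–18% |
| 20% | 5.6–7 | 27–32% |
| 30% | 8.4–10.5 | 36–45% |
| 50% | 14–17.5 | 60–71% |

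**4. Power of an interaction test.** With 28 per arm and prevalence p, SE = 0.48 × √[2/(28p) + 2/(28(1−p))], and power = Φ(0.415/SE − 1.96). For an interaction as large as the whole planned effect this gives 16% at p = 10%, 25% at 20%, 32% at 30% and 37% at 50%.

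**5. Chance of at least one false P<0.05, one outcome.**

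- Independent tests: 1 − 0.95⁷ = 30.2% for seven factors; 1 − 0.95⁵ = 22.6% for five.
- The factors are not independent: the composite is the union of the components, and the age classes exclude each other. Simulating no treatment effect (1,500 runs per scenario, cells too small to test left out) with assumed prevalences gave:

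| Scenario | Any of 7 interaction tests | Any within-stratum three-group test | High-risk patients per arm | Components (i)–(iii), patients per arm |
|---|---|---|---|---|
| Lower prevalences, 84 patients | 14.5% | 16.3% | 7.1 | 0.4–1.4 |
| Higher prevalences, 84 patients | 22.2% | 24.6% | 13.4 | 1.2–3.0 |
| Higher prevalences, 105 patients | 22.6% | 27.1% | 16.7 | 1.5–3.7 |

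Lower prevalences: family history 10%, polycystic kidney disease 5%, age 60 or over 5%, age 45–59 25%, triglycerides ≥200 mg/dL 20%, triglycerides 150–200 mg/dL 20%, BMI and HDL conditions 30% each. Higher prevalences, in the same order: 20%, 10%, 10%, 35%, 30%, 30%, 40% each.

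The overall range is about 15–27%, or roughly three to five times the nominal 5%.

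**6. Reach of the HDL limit.** Only patients aged 45–59 with triglycerides 150–200 mg/dL can be classified by it. Under the same assumptions that is 0.25 × 0.20 × 28 = 1.4 per arm at the lower prevalences, and 0.35 × 0.30 × 28 = 2.9 (or × 35 = 3.7) at the higher. Composite status changes for fewer still, because some of these patients qualify through another criterion.

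**The case against.** The strongest reply is that much of this concerns silence. How subgroups are tested, whether they are labelled exploratory and how multiplicity is handled are commonly left to an analysis plan, and the article does not say that each stratum will be tested on its own. That stands: the absence of an interaction test or a multiplicity adjustment is not in itself an error. What remains is stated text, namely a commitment to analyse every component and one significance rule covering the results.

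Some stronger readings are tempting but not supported:

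- *Chance findings are certain.* They are a risk of about 15–27% for one outcome, or 30% under independence. More outcomes or contrasts would raise it, but contrasts that share arms do not multiply the error by their number. The article names a comparison among three groups and no pairwise tests.
- *All subgroups hold a handful of patients.* Sparse cells are likely for the narrow components. Overall high-risk status had about 7–17 per arm in the scenarios above. No prevalence is given in the document.
- *The women's HDL limit is wrong, so women are misclassified.* The article does not show which limit, if either, is misprinted. The intended split may simply be redundant, and the cited sources are not at hand.
- *HDL is not available because Table 1 omits it.* Data Collection and Clinical Outcomes says laboratory data come from medical records, so the omission does not show this.

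**Conclusion.** The point holds in a limited form. The plan applies P<0.05 to one composite and four to six component subgroups in a trial sized for 28 evaluable patients per arm. At an assumed 5–20% prevalence a component has about 1–7 patients per arm and 8–32% power for the full planned effect. Low power is therefore at least as serious as false positives. These sizes rest on assumed prevalences, a two-sided 5% level and the planning SD of 0.48.

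The identical HDL limits are an anomaly on the page that needs reconciling. Their reach is small.

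Neither matter touches the primary comparison. Both are worth correcting because they concern stated rules and are cheap to change.

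**What to change.** - Keep one subgroup factor for testing: high versus not-high PTDM risk at baseline. Test it by a treatment-by-risk interaction in the primary model and label it exploratory. That test is itself weak (about 25–37% power at 20–50% prevalence for an interaction of 0.415), so its confidence interval should be reported.
- Report the components only as estimates with confidence intervals, without P<0.05 verdicts.
- Before analysis, check the HDL limits for men and women against cited sources 26–28. Then either correct the misprinted limit or drop the sex split.
- Put the component sentence in the future tense, since this is a plan.

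The cost is a few sentences of analysis wording and one checked threshold, with no change to recruitment, measurement or sample size. The downside is that component-level significance claims are given up.
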